## **8.4 Data Entry and Data Audit**

All sub-sites will be responsible for data entry, while the PUCRI-DM will be responsible for the data validation. The sub-sites shall follow the rules of a double blind recording method, with two data record staff entering the data at the same time. The PUCRI-DM will then check through and compare the records. For data that is inconsistent between the two records, the PUCRI-DM will verify and modify the data with reference to the paper CRF until both files in the database are identical. Should there be queries or abnormal values in the paper CRF during the data entry process, the PUCRI-DM will send these queries to the field researchers for answering.

## **8.5 Database Locking and Data Verification**

The research data will be frozen after the data of all participants have been entered and all queries have been addressed. Researchers will no longer be permitted to modify the data, so as to guarantee the stability of the research data.

The PUCRI-DM will draft the "Data Management Report" for the frozen database and submit it to the data review committee. Any possible problems with the data in the report will be resolved in a meeting where the researchers, statistician, and PUCRI-DM are present. A division of the

statistical population will also be conducted. The database will be locked should the researchers confirm that there are no queries with the data in the frozen database and the division of the statistical population is determined.

## 9. Statistical Analysis

### **Baseline Data Analysis:**

Participants will be described with respect to demographic information (age, gender, ethnic group, education, etc.), anthropometrics (weight, height, BMI, etc.), physical examination (SBP, DBP, etc.), life style and diet habits, labs (serum potassium, renal function, urinary sodium, urinary potassium, urinary microalbumin, etc.), comorbidities, medication history at baseline, both overall and separately for the intervention and control groups. Categorical data will be summarized by numbers and percentages. Continuous data will be summarized by mean, SD and range if data are normal and median, IQR and range if data are skewed. We will conduct one-way ANOVA on continuous variables and  $\chi^2$  test on categorical variables to check if the baseline characteristics balanced across randomized groups and to identify potential confounding variables.

**Effect Evaluation:** Results from ITT analysis will be reported as the primary result and the one from PP analysis will be reported as the secondary result.

Primary outcome is the change in SBP from baseline to follow-up

Secondary outcome includes change in DBP from baseline to follow-up, changes in 24-hr urinary sodium and urinary microalbumin; the risk of developing cardiovascular events

We will use multilevel mixed-effects model to control the cluster effect and confounding variables. We will compare the difference of changes in blood pressure before and after the intervention between SS and non-SS, SSSC and non-SSSC, SS + SSSC and SS only or SSSC only respectively.

### **Analysis for adherence:** Use ITT to analyze the results

We will use multilevel mixed-effects model to control the cluster effect and confounding variables. We will compare the changes in serum potassium levels before and after the intervention, changes in incidence of hyperkalemia before and after the intervention, and incidences of other possible adverse effect between SS and non-SS. We will use multilevel mixed-effects model to control the cluster effect and confounding variables. We will compare the changes in serum potassium levels before and after the intervention, changes in the incidence of hyperkalemia before and after the intervention, and incidences of other possible adverse reactions between SS + SSSC and SS only or SSSC only.

### **Safety Evaluation:** Use PP to analyze the results

Make use of a multilevel mixed-effects model to control the clustering effect and confounding variables. Compare the changes in blood potassium levels before and after the intervention, changes in the accumulated number of hyperkalemia incidences before and after the intervention, and incidences of other possible adverse reactions between SS and non-SS. Make use of a multilevel mixed-effects model to control the clustering effect and confounding variables. Compare the changes in blood potassium levels before and after the intervention, changes in the accumulated number of hyperkalemia incidences before and after the intervention, and incidences of other possible adverse reactions between SS + SSSC and SS only or SSSC only.

**Subgroup Analysis:**

Subgroup analysis will be conducted according to the baseline renal function (eGFR) stages to understand the effect modification of baseline renal function.

**Cost-effective analysis:**

A cost-effectiveness measure will be estimated based on the incremental cost of achieving each 1-mm Hg reduction in SBP. The cost is the fee (unit: Yuan )associated with intervention, including cost for salt substitute, faculty training, health education, diagnose and treatment for hyperkalemia. Incremental cost-effective ratio (ICER) will be calculated as below:

$$IC = \text{Cost initial} - \text{Cost complete}$$

$$IE = \text{SBP initial} - \text{SBP complete}$$

$$ICER = IC/IE$$

## 10. Sample Size Calculation

The research hypothesis is that the "salt substitute intervention would significantly reduce the systolic blood pressure of patients with hypertension", with the test power of 0.80 and the significance level at 0.05. According to previous studies, consuming salt substitutes for a prolonged period can lower the systolic blood pressure of patients with hypertension by roughly 2~5mmHg. This research hypothesizes that the systolic blood pressure of the elderly participants would decrease by 3.0mmHg, with a standard deviation of 18mmHg. Since the number of groups is 48 and the intra-group correlation coefficient is 0.02, 16 participants are needed in every group calculated by NCSS-PASS software. In addition, considering that about 20% of the participants might be lost to follow-up or be removed from the research due to non-compliance, it is finally determined that 20 participants will be included in each nursing home, for a total of 960 participants across 48 nursing homes.

Based on the sample size calculated above, the sample size for the four intervention groups is as follows:

|                   |     | SS intervention |     |       |
|-------------------|-----|-----------------|-----|-------|
|                   |     | Yes             | No  | Total |
| SSSC intervention | Yes | 240             | 240 | 480   |
|                   | No  | 240             | 240 | 480   |
| Total             |     | 480             | 480 | 960   |

For the other intervention strategy, it can be estimated from the previous research experience that the SSSC intervention strategy can reduce the systolic blood pressure of the elderly by 4.0mmHg. With the significance level, number of groups, and intra-group correlation coefficient constant, and based on the sample size calculated above, it can be concluded that the power of applying this intervention strategy to reducing systolic blood pressure by 4.0mmHg will be 96.6%.

Given the potential changes of actual systolic blood pressure difference during the trial and the number of participants recruited from each facility, the changes to the trial power will follow the trend below:

[figure not shown]

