## **2.5 Sample size**

The study was designed to provide at least 80% power (with a 2-sided  $\alpha = 0.05$ ) to detect a net reduction in mean SBP of at least 3.0 mm Hg between groups with either or both interventions compared to control. The power estimate assumed a standard deviation of systolic blood pressure of 18 mmHg based on previous studies, an intra-cluster correlation coefficient of 0.02, and a loss of follow-up rate of 20%, resulting in a sample size of 960 individuals drawn from 48 clusters, each with 20 participants.

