### **3.1 Confidence intervals and p values**

All applicable statistical tests will be 2-sided and will be performed using a 5% significance level. All confidence intervals presented will be 95% and two-sided.

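### Protocol section 10's 16 per facility and 96.6% power reproduce only with 48 facilities in each comparison group; the trial has 24 against 24, which on the same inputs gives about 51% and 75%

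*Supplement*

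**What the plan says.** Protocol V1.4 section 10 sizes the trial on the salt-substitute (SS) comparison "with the test power of 0.80 and the significance level at 0.05". It assumes that SBP "would decrease by 3.0mmHg, with a standard deviation of 18mmHg". It then reasons that since "the number of groups is 48 and the intra-group correlation coefficient is 0.02, 16 participants are needed in every group", 20 should be enrolled per home to allow for 20% loss, making 960 participants in 48 homes. Its table divides the 960 into 480 v 480 at each factorial margin. For stepwise salt supply control (SSSC), keeping the other inputs, it concludes that "the power of applying this intervention strategy to reducing systolic blood pressure by 4.0mmHg will be 96.6" per cent.

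SAP 2.4 randomises the 48 facilities equally to the four arms. SAP 2.5 states "The study was designed to provide at least 80% power" for a 3.0 mmHg net reduction, "resulting in a sample size of 960 individuals drawn from 48 clusters, each with 20 participants", and ties this to groups receiving one or both strategies set against the control group. SAP 3.1 makes all tests two-sided at 5%. The primary models in SAP 5.1.1 compare facilities that receive a given intervention with those that do not. They adjust for baseline SBP and use the follow-up SBP measurements at months 6, 12, 18 and 24.

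**The concern.** With 48 facilities allocated equally to four arms, each arm has 12 and each main-effect comparison sets 24 against 24. Sixteen evaluable residents in each of 24 facilities, at SD 18 and ICC 0.02, looks far too few for 80% power at 3.0 mmHg. The pattern suggests that the total number of facilities was used as the number per comparison group, which would double the clusters credited to each comparison.

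Section 10 is the numerical justification for both primary aims, and SAP 2.5 repeats it. It also gives near-certain power for SSSC, which SAP 5.1.1 calls the only novel intervention. If that basis is wrong, readers of a null result are told that the trial was better placed to detect the target effect than its stated inputs support.

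**Working it through.** **Inputs.** SD 18 mmHg, ICC 0.02, 16 evaluable per facility, effects of 3.0 and 4.0 mmHg, alpha 0.05 (Protocol section 10); two-sided (SAP 2.5 and 3.1); 48 facilities in total, allocated equally to four arms (SAP 2.4).

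**Formula.** With k facilities per comparison group and m evaluable per facility:

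- design effect DE = 1 + (m − 1) × ICC = 1 + 15 × 0.02 = 1.30
- SE = SD × √(2 × DE / (k × m))
- power from a noncentral t on 2(k − 1) df; the normal approximation (z) is given alongside.

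**Step 1: reproduce the stated figures.** With k = 48 per group:

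- m = 16: SE = 18 × √(2.60 / 768) = 1.047. Power at 3.0 mmHg is 80.9% (z 81.7%).
- m = 15: 79.0% (z 79.8%). So 16 is the smallest m that reaches 80%, as stated.
- m = 16, 4.0 mmHg: 96.56%, the stated 96.6%.

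This requires 96 facilities.

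**Step 2: the actual design.** With k = 24 per group and m = 16, SE = 18 × √(2.60 / 384) = 1.481.

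| Effect | Stated | t, 46 df | z |
|---|---|---|---|
| 3.0 mmHg | 80% | 50.9% | 52.6% |
| 4.0 mmHg | 96.6% | 75.3% | 77.1% |

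The difference detectable with 80% power is 4.24 mmHg by t, or 4.15 by z (2.80 × 1.481).

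**Step 3: other readings at 24 v 24.** None gives both stated figures.

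| Variant | 3.0 mmHg | 4.0 mmHg |
|---|---|---|
| All 20 per facility evaluable | 57.6% | 81.8% |
| ICC 0, m = 16 | 61.8% | 85.4% |
| ICC 0, m = 20 | 71.5% | 92.1% |
| One-sided test, m = 16 | 63.7% | 84.5% |

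**Step 4: the SAP 5.1.1 model.** The documents give no within-person correlation ρ, so this step rests on assumptions: compound symmetry, ρ from 0.3 to 0.7, the same effect at every visit, 16 evaluable per facility, and no reduction of the between-facility variance by baseline adjustment. The total variance of 324 splits into 0.02 × 324 = 6.48 between facilities and 317.52 within.

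- SE² = 2 × (6.48 + 317.52 × f / 16) / 24
- four visits, baseline-adjusted: f = (1 + 3ρ)/4 − ρ²
- month 24 alone, baseline-adjusted: f = 1 − ρ²

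| ρ | f, four visits | SE | 3.0 mmHg | 4.0 mmHg | f, month 24 | SE | 3.0 mmHg |
|---|---|---|---|---|---|---|---|
| 0.3 | 0.385 | 1.085 | 77% | 95% | 0.91 | 1.430 | 54% |
| 0.5 | 0.375 | 1.077 | 78% | 95% | 0.75 | 1.334 | 60% |
| 0.7 | 0.285 | 1.006 | 83% | 97% | 0.51 | 1.176 | 70% |

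**The case against.** The strongest reply is that 51% and 75% describe an analysis the SAP does not run. They come from one unadjusted comparison of means, whereas SAP 5.1.1 adjusts for baseline and pools four visits. Under the assumptions in step 4 its power is close to the stated 80% and 96.6%. The full-analysis set needs only one post-baseline reading, so more than 16 per facility may contribute; with 20, the same assumptions give 82-87% and 97-98%. This stands. A reader might infer that the trial really has about even odds of detecting 3 mmHg; the documents do not support that.

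It does not rescue the text as written. Neither document claims credit for baseline adjustment or repeated visits in its power statement. Both rest the 80% on SD 18, ICC 0.02 and 48 clusters, which do not yield it. Protocol section 6.1 still defines the primary outcome as the change to month 24, where baseline-adjusted power at 3.0 mmHg is about 54-70%. SAP 5.9 explains the move to repeated measures by missing data, not power. A constant effect is also generous for SSSC: its targets step down over 18 months after a preparatory month, and SAP 5.7 allows that it may take months to act.

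Second, no passage says that 48 was entered per group. The software settings are not given, so the mechanism is inferred. The inference is strong, because both V1.4 figures match closely and no variant tried at 24 v 24 matches both.

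Third, SAP 2.5's wording might be read as a promise of 80% for a single arm against control. That would be 12 v 12 facilities, with about 28% power at 3.0 mmHg (z 30%). The primary models do not test that contrast, so this is a wording fault, not the power of a primary test.

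Finally, estimates will be reported with 95% confidence intervals, and no decision rule depends on the stated power. This limits the harm but does not make the figures correct.

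**Conclusion.** The concern holds as an error in the power justification. Section 10's stated 16 per facility and 96.6% reproduce only with 48 facilities in each comparison group, twice what the design has. On section 10's own inputs, 24 v 24 gives about 51% at 3.0 mmHg and 75% at 4.0 mmHg, with about 4.2 mmHg detectable at 80% power. SAP 2.5 repeats an 80% that its listed inputs do not support, and attaches it to a contrast other than the one the primary models test.

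The conclusion is about what the stated inputs deliver, not the power of the final analysis. For the SAP's model, power may be near the stated values, but only under a correlation and a constant-effect assumption that neither document states.

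**What to change.** **Protocol section 10.** State that each factor level has 24 facilities. On the listed inputs, give power as about 51% at 3.0 mmHg and about 75% at 4.0 mmHg, and the difference detectable with 80% power as about 4.2 mmHg. Check the accompanying power figure against the 24 v 24 design and correct it.

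**SAP 2.5.** Replace the wording about one or both strategies against control with the two 24 v 24 comparisons. Replace the basis of the 80% with power for the SAP 5.1.1 model (baseline-adjusted, months 6 to 24), stating the assumed within-person correlation and its source. If no estimate is available, show the 0.3 to 0.7 range: about 77-83% at 3.0 mmHg and 95-97% at 4.0 mmHg, with about 54-70% at 3.0 mmHg for month 24 alone. State that the constant-effect assumption is generous for SSSC, which phases in over 18 months.

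**Cost.** Two paragraphs reworded and one figure checked. No extra participants and no change to conduct or analysis. The power statement becomes less favourable in the protocol and more conditional in the SAP.

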## **11. Quality Control**

### **11.1 Modifications to the Protocol**

The protocol must not be freely modified once it has been approved. If the protocol must be modified after the trial has started because of special cases such as difficulty in execution, an agreement has to be reached by the advisory committee after they discuss the matter. Only then can the protocol be modified or supplemented. The modified content has to be recorded in writing.

The process for modifying the protocol is as follows:

- Noticing that there is a clear problem and understanding the need to modify the protocol;
- Calling for a meeting of the advisory committee to discuss the matter and suggest a way to resolve the issue;
- Principal investigator signs and creates the "Protocol Modification Instructions";
- The modified protocol and "Protocol Modification Instructions" have to be sent to the Ethics Committee for approval or be put on record;
- The modified protocol can be executed after obtaining the approval of the Ethics Committee.

### **11.2 Training**

The principal investigator is responsible for creating a training plan for the project-related personnel. The experts and project manager appointed by the principal investigator will organize the training, complete the training records, and take custody of the training records in the project management document. All relevant research personnel shall receive their respective training to ensure that they are qualified to undertake the specific tasks assigned to them. The contents of the training for different research personnel are as follows:

- GCP: Principal investigator, managers of all partner organizations, and all staff members
- Subject protection and ethical requirements, including the signing requirement of informed consent, SAE, as well as the handling of protocol violation (PV) and the report requirements: Principal investigator and all staff members
- Research protocol: Principal investigator and all staff members
- Standard operating procedures for the trial, including intervention strategies, trial operation-related standard operating procedures such as blood pressure measurement and testing for 24-hr urinary sodium: Staff members responsible for and participating in the corresponding work
- Instructions on filling up the CRF: Staff members assigned for questioning and filling out the relevant forms

- Things to note on the implementation of the clinical research (e.g. selection of nursing homes and participants, inclusion and follow-up process, etc.): All field staff members
- Project workplan: Principal investigator and all the managers of participating organizations

Aside from these, the principal investigator and project coordinator can increase the training contents if needed during the whole course of the trial. For example, training on the weak links of the trial, training on updation of the protocol, and various targeted trainings on the standard operation procedures.

### **11.3 Monitoring**

The PUCRI will designate a project specialist to monitor this trial, with the main aim of confirming whether the implementation of the trial, data record and analysis conform to the trial protocol and the relevant rules and regulations. Investigator should fully cooperate with the project specialist.

The project specialist will supervise and visit the research sites based on the "Monitoring Plan" that is drawn up beforehand. This will be done either through on-site visits or off-site visits. The contents of the supervision include:

- Completion and updation of the research document;
- Signing of informed consent form;
- Source data verification;
- Distribution and management of the salt substitute;
- Stock in and stock out records for salt and other foods with high-salt content of various nursing homes;
- The implementation of blood potassium monitoring plan for hyperkalemic participants and participants in the high-emphasis monitoring group;
- Occurrence, handling and reporting of SAEs and PVs;

The project specialist will complete a written monitoring report after every visit. The monitoring report will be submitted to all parties involved in project management as required by the "Monitoring Plan".

### **11.4 Quality Control for Data**

A project specialist from the PUCRI will review the completeness and accuracy of the CRF data that is recorded by the researchers according to the monitoring plan. He/she will also guide the staff member who input the data on revising or adding data based on the requirements. The data

management specialist from the PUCRI will conduct a logic check on the logical relationship of the CRF data, whether or not the data goes against the protocol, and whether or not it exceeds the normal range of reference. He/she will create a query table for incomplete, missing, or illogical data and request researchers to address, confirm, or correct the data in question. The database can only be locked and analyzed after all of the queries behind the data have been resolved.

## **12. Subject Protection**

### **12.1 Ethics Review**

This research protocol will be submitted to the PKU IRB for review and continuous review. It includes the completed research protocol, CRF, informed consent form, and other documents. The clinical trial can only be commenced after obtaining approval from the IRB. Throughout the implementation of the research, researchers shall abide by the ethical requirements of the GCP and the Declaration of Helsinki and guarantee the rights of the participants. We will regularly submit a research progress report as requested by the IRB and report the state of the research implementation in a timely manner.

### **12.2 Informed Consent**

This research will seek informed consent from the managers of the nursing homes and all elderly staying in the nursing homes. The informed consent of the nursing homes will be obtained through a partnership agreement with the nursing home. Whether it is from the nursing home or the elderly, the researchers should give a detailed introduction on the purpose of the research, research methods, potential benefits and risks, and what kind of cooperation is expected from them when obtaining the informed consent form. The researchers should also tell them that participating in this clinical research is completely voluntary, that they can withdraw from the experiment at any time, and that refusing or withdrawing from the trial will not affect the treatment or reasonable medical rights of the elderly. The researchers have to address any questions that the other party might have during the process and give the elderly enough time to consider and discuss with their family members. The researchers should also confirm that the other party has decided on their own whether or not to participate in the research after they have a sufficient understanding of the research. Should the elderly be willing to participate in the research, they will be required to sign a hardcopy informed consent form. Illiterate elderly can use their fingerprints or appoint someone to sign on their behalf. The researchers who have obtained informed consent will also have to sign and state the date of signature on the informed consent form at the same time as the other party. The elderly will receive a copy of the informed consent

form. The original document will be appropriately kept by the researchers as part of the clinical research documents. Should there be a need to modify the protocol during the research implementation, or if new information is obtained that might influence the participants' continued participation in the research, the researchers have to make the appropriate modification to the informed consent form and seek informed consent from the participants again.

